# A perioperative surgeon-controlled open-lung approach versus conventional protective ventilation with low positive end-expiratory pressure in cardiac surgery with cardiopulmonary bypass (PROVECS): study protocol for a randomized controlled trial

**DOI:** 10.1186/s13063-018-2967-y

**Published:** 2018-11-13

**Keywords:** Postoperative pulmonary complications, Cardiac surgery, Cardiopulmonary bypass, Mechanical ventilation, Positive end-expiratory pressure

## Abstract

**Background:**

Postoperative pulmonary complications (PPCs) are frequent after on-pump cardiac surgery. Cardiac surgery results in a complex pulmonary insult leading to high susceptibility to perioperative pulmonary atelectasis. For technical reasons, ventilator settings interact with the surgical procedure and traditionally, low levels of positive end-expiratory pressure (PEEP) have been used. The objective is to compare a perioperative, multimodal and surgeon-controlled open-lung approach with conventional protective ventilation with low PEEP to prevent PPCs in patients undergoing cardiac surgery.

**Methods/design:**

The perioperative open-lung protective ventilation in cardiac surgery (PROVECS) trial is a multicenter, two-arm, randomized controlled trial. In total, 494 patients scheduled for elective cardiac surgery with cardiopulmonary bypass (CPB) and aortic cross-clamp will be randomized into one of the two treatment arms. In the experimental group, systematic recruitment maneuvers and perioperative high PEEP (8 cmH2O) are associated with ultra-protective ventilation during CPB. In this group, the settings of the ventilator are controlled by surgeons in relation to standardized protocol deviations. In the control group, no recruitment maneuvers, low levels of PEEP (2 cmH2O) and continuous positive airway pressure during CPB (2 cmH2O) are used. Low tidal volumes (6–8 mL/kg of predicted body weight) are used before and after CPB in each group. The primary endpoint is a composite of the single PPCs evaluated during the first 7 postoperative days.

**Discussion:**

The PROVECS trial will be the first multicenter randomized controlled trial to evaluate the impact of a perioperative and multimodal open-lung ventilatory strategy on the occurrence of PPCs after on-pump cardiac surgery. The trial design includes standardized surgeon-controlled protocol deviations that guarantee a pragmatic approach. The results will help anesthesiologists and surgeons aiming to optimize ventilatory settings during cardiac surgery.

**Trial registration:**

Clinical Trials.gov, NCT 02866578. Registered on 15 August 2016. Last updated 11 July 2017.

**Electronic supplementary material:**

The online version of this article (10.1186/s13063-018-2967-y) contains supplementary material, which is available to authorized users.

## Background

Postoperative pulmonary complications (PPCs) remain a frequent event after on-pump cardiac surgery [1]. PPCs are responsible for significant morbidity and mortality [2]. They are mostly characterized by transient hypoxemia (up to 25%) while acute respiratory distress syndrome and postoperative pneumonia are less frequently encountered [3]. The use of high-flow nasal oxygen therapy and non-invasive ventilation is necessary to treat the most severe forms of respiratory failure [4], leading to prolonged stays in both the intensive care unit (ICU) and in hospital in general.

General anesthesia with invasive mechanical ventilation induces its own lung insult, which has been widely described as ventilator-induced lung injury [5]. A second pulmonary hit is more specific to cardiac surgery. Cardiopulmonary bypass (CPB) effectively activates a systemic inflammatory response [6] and the aortic cross clamp is responsible for lung ischemic injury [7]. Moreover, complete sternotomy, frequent blood transfusions and postoperative pain are involved in the high incidence of PPCs [8–10]. At the pulmonary level, cardiac surgery is related to increased permeability of the alveolo-capillary barrier [11, 12] and mucociliary dysfunction [13]. Pulmonary atelectasis is very common in this context, [14, 15].

Preventing PPCs with specific perioperative ventilatory management is not a new approach [16]. Many reports have described the concept of protective ventilation [17, 18]. Inspired by the results obtained in critical care medicine in patients with acute respiratory distress syndrome (ARDS) [19], the use of low tidal volumes (6–8 mL/kg predicted body weight) has spread to the operating theater [20–22] and there is now an established consensus [23]. However, the use of low tidal volumes may precipitate the constitution of pulmonary atelectasis in the poorly ventilated, dependent regions of the lung [16]. The open-lung approach corresponds to the use of systematic recruitment maneuvers (“open the lung”) associated with high levels of end-expiratory pressure (“keep it open”) in order to prevent atelectasis [24]. The efficacy of the open-lung approach in preventing atelectasis has been well-described in cardiac surgery preclinical studies [25, 26]. Nonetheless, the clinical effectiveness of open-lung ventilation during general anesthesia [23] or in patients with ARDS [27] is still a matter of debate. The largest randomized trials evaluating the open-lung approach during abdominal surgery [28, 29] have not found any benefit in using recruitment maneuvers and higher positive end-expiratory pressure (PEEP). The theoretical interest of preventing pulmonary atelectasis during the mechanical ventilation phase could be lost after tracheal extubation, when PPCs appear. Moreover, the hemodynamic safety of high ventilatory pressure has been questioned [29, 30].

In cardiac surgery, high levels of PEEP have not historically been used because of the technical interference induced by the movements of the lung in the operative field, particularly in the case of a pleural opening. Moreover, the hemodynamic consequences may be more severe in patients undergoing cardiac surgery. During CPB, lung ventilation is still widely interrupted because of the absence of lung perfusion and for surgical comfort [31]. Maintaining lung ventilation with or without perfusion has shown positive effects on the inflammatory response [32] and on post-CPB gas exchange [33, 34]. However, this effect seems to be short term and there is no sufficient clinical evidence to support specific ventilatory management during CPB [35]. Regarding the high incidence of pulmonary atelectasis in cardiac surgery, the benefit of a multimodal and perioperative open-lung approach, including lung ventilation during CPB, has been suggested [36]. However, because of the potential impact on the surgical procedure and cardiac function, the use of open-lung ventilation in cardiac surgery needs to be justified by the highest level of clinical evidence. We hypothesize that using systematic recruitment maneuvers, higher PEEP and ventilation during CPB will prevent PPCs after cardiac surgery. We will compare a perioperative open-lung approach involving surgeon-controlled maximization of alveolar recruitment with the conventional low-PEEP strategy.

The primary objective is to assess the efficacy of the perioperative open-lung strategy in terms of PPC incidence; the secondary objectives are to assess the use of specific ventilatory support, postoperative extra pulmonary complications, adverse events and the number of ICU-free days by postoperative day 7.

## Methods/design

### Design

PROVECS is a prospective, multicenter, randomized, controlled, two-arm trial comparing two perioperative ventilatory strategies in cardiac surgery with cardiopulmonary bypass: (1) experimental strategy: surgeon-controlled open-lung ventilation; (2) control strategy: conventional protective ventilation with low PEEP (Fig. 1). Double-blinding is ensured by the general anesthesia in the trial participants, and by masking the outcome assessor. Hiding all the intraoperative data (including ventilator settings) on the electronic case report form (CRF) at the end of surgery ensures the masking of the treatment arm Additional file 1. A checklist of recommended items to address in a clinical trial protocol according to the "Standard Protocol Items: Recommendations for Interventional Trials (SPIRIT) 2013 is provided in Additional file 2.

**Fig. 1 Fig1:**
[figure not shown]
Consolidated Standards of Reporting Trials (CONSORT) diagram for the PROVECS trial. BMI body mass index

### Study population

#### Inclusion criteria

Patients are eligible if they are scheduled for elective cardiac surgery with general anesthesia, invasive mechanical ventilation, conventional CPB, aortic cross clamp and complete median sternotomy. All patients will be included after providing written, signed, informed consent. Eligible surgeons are defined as cardiac surgery physicians licensed for at least 2 years, working in high-volume university hospital centers with a minimum of 400 surgical operations with CPB each year.

#### Exclusion criteria

The exclusion criteria are surgery or patient related. The surgery-related criteria are:Emergent surgery including cardiac transplantation, aortic dissection and active endocarditis surgeryLeft ventricular assist device implantationSurgery with circulatory arrestRedo surgery

The patient-related criteria are:Age < 18 yearsAcute or chronic hypoxemia defined by partial pressure of arterial oxygen (PaO2) < 65 mmHg or pulse oximetry < 95% on ambient airMechanical ventilation in the 7 days prior to surgeryPreoperative shockBody mass index (BMI) > 35 kg/m^2^Obstructive sleep apnea syndrome treated with continuous positive airway pressurePreoperative left ventricular ejection fraction < 40%Right ventricular systolic dysfunction (Doppler-derived tricuspid lateral annular systolic velocity < 10 cm∙s^− 1^)Systolic pulmonary artery pressure > 50 mmHgGlomerular filtration rate < 30 mL∙min^− 1^

### Interventions

Mechanical ventilation is performed with anesthesia and ICU ventilators set on volume-controlled ventilation. All patients are ventilated with low tidal volumes before and after the CPB (6–8 mL/kg of predicted body weight). The predicted body weight is calculated with the formula: 50 + 0.91 × (Height in cm – 152.4) in men and 45.5 + 0.91 × (height in cm – 152.4) in women. The respiratory rate will be freely adjusted before and after CPB by the anesthesiologist to maintain end-tidal CO2 partial pressure between 35 and 45 mmHg. The lowest fraction of inspired oxygen (FiO2) will be targeted in both groups to maintain SpO2 > 94%. The inspiratory to expiratory ratio (I:E) is set at 1:2 (Table 2).

**Table 2 Tab2:** Perioperative ventilatory protocol in each of the two treatment arms

	Conventional ventilation	Open-lung ventilation
Ventilation before CPB	• Tidal volume 6–8 mL/kg PBW • PEEP 2 cmH2O • RR for ETCO2 35–45 mmHg • Lowest FiO2 to maintain SpO2 > 94%. • I:E ratio at 1:2	• Tidal volume 6–8 mL/kg PBW • PEEP 8 cmH2O • RR for ETCO2 35–45 mmHg • Lowest FiO2 to maintain SpO2 > 94% • I:E ratio at 1:2
Systematic recruitment maneuvers	No	Yes
Ventilation during CPB	CPAP 2 cmH2O	Ultraprotective ventilation • Tidal volume 3 mL/kg PBW • PEEP 8 cmH2O • RR 12 cpm • FiO2 40%
Ventilation after CPB (including in ICU)	• Tidal volume 6–8 mL/kg PBW • PEEP 2 cmH2O • RR for ETCO2 35––45 mmHg • Lowest FiO2 to maintain SpO2 > 94% • I:E ratio at 1:2	• Tidal volume 6–8 mL/kg PBW • PEEP 8 cmH2O • RR for ETCO2 35––45 mmHg • Lowest FiO2 to maintain SpO2 > 94% • I:E ratio at 1:2
Protocol deviation	Rescue strategy • Unplanned recruitment maneuver • +/− PEEP increase	Surgical or hemodynamic deviation • Recruitment maneuver interruption • PEEP decrease (1 cmH2O by 1 cmH2O step)

*CPB* cardiopulmonary bypass, *CPAP* continuous positive airway pressure, *FiO2* inspired oxygen fraction, *I:E* inspiratory time to expiratory time ratio, *PEEP* positive end-expiratory pressure, *PBW* predicted body weight, *RR* respiratory rate, *SpO2* pulse oximetry, *ETCO2* end-tidal CO2

#### Experimental strategy: Surgeon-controlled open-lung ventilation

In the experimental open-lung group, recruitment maneuvers (continuous positive airway pressure maintained at 30 cmH2O for 30 s) are systematically implemented at predefined stages in the surgical procedure:After intubation and invasive arterial line placementAfter CPB initiation when targeted blood-flow is reachedBefore aortic de-clamping, after standard balloon de-airing maneuversAt ICU arrival with the ICU ventilatorAfter each breathing circuit disconnection

PEEP levels in the experimental open-lung group are set at 8 cmH2O from intubation in the operating room to extubation in the ICU. During CPB, ultraprotective ventilation is used with PEEP at 8 cmH2O, very low tidal volumes (3 mL/kg of predicted body weight), a respiratory rate of 12 cycles per minute and FiO2 of 40%. Surgical protocol deviation has been standardized (see below and Table 2).

#### Control strategy: conventional protective ventilation with low PEEP

No recruitment maneuvers are carried out. The PEEP is set at 2 cmH2O from intubation to extubation. Continuous positive airway pressure is maintained at 2 cmH2O during CPB (Table 2).

### Protocol deviation

In the experimental strategy group, the recruitment maneuver before and after the CPB can be avoided or interrupted on surgical demand or in the case of systolic arterial pressure < 80 mmHg despite the adequate use of fluids and/or vasoactive drugs. The recruitment maneuver during CPB can be interrupted on surgical demand, or in case of a severe decrease in venous return with the inability to maintain the blood flow. PEEP levels can be decreased on surgical demand or on the anesthesiologist’s decision in the case of hemodynamic impairment despite the adequate use of fluids and/or vasoactive drugs. In these cases, PEEP will be decreased in stages of 1 cmH2O until correction of the problem. In the conventional strategy group, in the case of intraoperative hypoxemia (SpO2 < 92% despite FiO2 80%), unplanned recruitment maneuvers and/or increased PEEP are permitted as a rescue strategy at the anesthesiologist’s discretion (Table 2). Data on deviations from the protocol (including the number of completed recruitment maneuvers and effective intraoperative PEEP levels) will be analyzed (Fig. 2).

**Fig. 2 Fig2:**
[figure not shown]
PROVECS trial schedule during the study period. *eCRF* electronic case report form, *HFNO* high-flow nasal oxygen therapy, *ICU* intensive care unit, *IMV* intensive mechanical ventilation, *NIV* non-invasive ventilation, *PaO2* arterial pressure in oxygen, *POD* postoperative day, *SpO2* pulse oximetry

### Standard procedures

#### Screening and inclusion

Patients are screened for inclusion and exclusion criteria during the preoperative visit with the anesthesiologist. In the absence of exclusion criteria, patients are included after providing written, signed, informed consent.

#### Randomization

Computer-generated randomized lists will be drawn up by an independent operator before the beginning of the study, using a permuted block design. The allocation sequence is stratified by center (1:1 allocation ratio) and sequentially numbered. The allocation is implemented automatically in the electronic case report form (CleanWEB™, Telemedicine Technologies S.A.S., Boulogne-Billancourt, France). The anesthesiologist in charge will assign a patient to the intervention when the patient is in the operating room with a confirmed indication for surgery.

#### Surgery

The type of drugs used for the anesthesia, the management of the CPB and fluid and transfusion strategies are implemented according to local protocols in each recruiting center. Nonetheless, the use of peridural thoracic anesthesia is not permitted. During sternal sawing, PEEP will be temporarily set to 0 cmH2O in both groups in order to prevent unnecessary pleural opening. Before aortic declamping, de-airing maneuvers with manual balloon ventilation are performed in both groups according to local protocols, with or without the use of transesophageal echocardiography and under surgical guidance.

#### Follow up

During transport from the operating room to the ICU, ventilation is operated with a self-inflating balloon or transport ventilator. If the transport ventilator is used, respiratory parameters are set according to the allocated treatment arm. A fast-track extubation protocol, defined by extubations performed before the 6th postoperative hour, is followed in all centers. The postoperative care, including sedation drugs, analgesia, fluid management, respiratory physiotherapy and the duration of the stay in the ICU, is performed according to local protocols and at the discretion of the physician in charge. The postoperative use of curative non-invasive ventilation or nasal high-flow oxygen therapy is implemented according to local protocols in each recruiting center. “Prophylactic” use (before any type of respiratory failure) of these techniques is not permitted. New invasive mechanical ventilation will be indicated at the discretion of the ICU physician in charge. The minimal ICU length of stay is 24 h.

### Study endpoints

The primary endpoint, the proportion of PPCs, is defined as a composite endpoint taking the presence of at least one of the following items during the first 7 postoperative days into account. These PPCs have been defined, in accordance with previous or ongoing studies [20, 29, 37], as follows:Mild respiratory failure: SpO2 < 90% or PaO2 < 60 mmHg after breathing ambient air for 10 min (excluding hypoventilation) and corrected with an oxygen supply of 1–3 L/min with a nasal cannulaModerate respiratory failure: SpO2 < 90% or PaO2 < 60 mmHg despite a 3 L/min oxygen supply with a nasal cannula (excluding hypoventilation) and corrected with an oxygen supply from 4 to 10 L/min with a face mask.Severe respiratory failure: SpO2 < 90% or PaO2 < 60 mmHg despite a 10 L/min oxygen supply with a face mask (excluding hypoventilation) and corrected with an oxygen supply > 10 L/min with a high-flow face mask or with non-invasive ventilation or with high-flow nasal oxygen therapy or with invasive mechanical ventilationFast-track extubation failure associated with hypoxemia: delayed extubation after the first 6 h postoperative, associated with PaO2/FiO2 < 300New invasive mechanical ventilation associated with hypoxemia, defined as PaO2/FiO2 < 300Bronchospasm: new wheezing, indicating bronchodilator treatment (except preoperative chronic obstructive pulmonary disease (COPD) or asthma)Severe tracheobronchial congestion: audible ronchi associated with disturbance in respiratory mechanicsPost-extubation respiratory acidosis defined by pH ≤ 7.30 and PaCO2 > 45 mmHgSuspected pneumonia: new pulmonary infiltrate on a chest x-ray, plus at least two of the following: temperature > 38.5 °C or < 35.5 °C, leukocytosis or leukopenia (white blood cells > 12,000 cells/mm^3^ or < 4000 cells/mm^3^), purulent secretions and antibiotic treatmentConfirmed pneumonia: new pulmonary infiltrate on a chest x-ray plus microbiological documentation (> 10^7^ CFU/mm^3^ on expectorated sputum, > 10^5^ CFU/mm^3^ on trans-tracheal aspiration or > 10^4^ CFU/mm^3^ on bronchoalveolar lavage)Pleural effusion with need for further postoperative pleural drainageRadiological atelectasis: new lung opacity on a chest x-ray with a shift in the mediastinum or ipsilateral hemi-diaphragmAcute respiratory distress syndrome (ARDS) as defined by the Berlin definition [38].

The secondary clinical endpoints include:Each preceding PPC by postoperative day 7 analyzed individuallyUse of non-invasive ventilation by postoperative day 7Use of high-flown nasal oxygen therapy by postoperative day 7Use of new invasive mechanical ventilation by postoperative day 7Postoperative extrapulmonary complications analyzed individually by postoperative day 7Systemic inflammatory response syndrome, sepsis and septic shock (as defined in [39])Postoperative wound infection (sepsis with purulent wound drainage and antibiotic administration)Postoperative pericardial tamponade (need for re-intervention)De novo postoperative atrial fibrillationCardiogenic pulmonary edema (acute hypoxemia with diffuse bilateral pulmonary infiltrate on a chest x-ray, high left atrial pressure on cardiac ultrasound or pulmonary capillary wedged pressure > 18 mmHg)Acute kidney injury (Kidney Disease: Improving Global Outcomes (KDIGO) stage 2 or 3)Delirium (disturbed state of consciousness and cognitive dysfunction with or without agitation)6.Adverse events by postoperative day 7:postoperative pneumothorax (need for further postoperative pleural drainage)use of intraoperative or postoperative vasoactive drugs (excluding ephedrine and phenylephrine)use of high-dose inotropes (> 8 μg∙kg^− 1^∙min^− 1^ of dobutamine or > 0.8 μg∙kg^− 1^∙min^− 1^ of milrinone)acute postoperative bleeding with need for re-intervention before the 12th postoperative hour7.Survival in terms of ICU-free days by postoperative day 78.Global mortality by postoperative day 7

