### Sample size and power

The sample size was determined to obtain 80% power to detect a 10-point difference between the two groups in the occurrence of PPCs at day 7 (25% in the control strategy group vs 15% in the experimental strategy group). This difference is based on previous reports [1, 3, 10] and has been considered to be clinically significant. With the threshold for statistical significance set at a *P* value of 0.05, these calculations showed that 494 patients are needed (247 per group, Fig. 1). As patients will be allocated in the operating room after confirmation of the indication for surgery and followed during the 7 postoperative days in the ICU and surgical ward, a very low dropout rate is expected.

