### Statistical analysis

The data will be analyzed using SPSS version 17.0 software. Patients who have at least one of the following conditions will be not included in the final analysis: patients inappropriately included despite providing consent, and patients who remove their consent. The primary analysis will be carried out according to the intention-to-treat principle. The full analysis population (including all subjects who will be randomized and will be at least evaluated at baseline) will be used in the primary analysis. No interim analysis is planned. A flow chart will be provided. The normality of the parameters will be estimated using frequency histograms and the Shapiro test. The baseline and intraoperative parameters will be described per group (“control” and “experimental”) in accordance with the Consolidated Standards of Reporting Trials (CONSORT) guidelines [40]. The proportion of PPCs at 7 postoperative days will be calculated and compared between the two groups (control and experimental) using the chi-square test or Fisher’s exact test for categorical variables (primary analysis). Multivariate analysis (secondary analysis) using logistic regression models will be performed to determine variables potentially linked to the occurrence of PPCs. Variables relevant to the models will be selected based on their clinical significance and/or a threshold *P* value ≤0.1 in the univariate analysis. The final models will estimate the odds ratios and 95% confidence intervals. The proportions of each secondary endpoint (each postoperative pulmonary complication, non-pulmonary complication, use of new invasive and non-invasive ventilation, use of high-flow nasal oxygen therapy, adverse event) will be compared between the groups. Multiple comparison corrections will be performed for non-independent outcomes. ICU-free days will be compared between the two groups. A potential center effect will be assessed by mixed effects modeling using generalized linear mixed model (SAS software, 9.4 version, GLIMMIX procedure; center as a random effect); the result will be presented as the odd ratio and its 95% CI. All of the tests will be two-tailed with a 5% significance level.

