We opted for a binary collapsed composite of single PPCs that have a real clinical meaning in daily practice. With a consensual and unambiguous definition of PPCs, we facilitate the assessment of the primary outcome, prevent the risk of wrong diagnoses and allow for comparisons with previous or ongoing studies [20, 28, 29, 37]. For example, the “respiratory failure” outcome, based on hypoxemia evaluated with SpO2 tolerance to room air ventilation, has previously been described in different trials interested in PPCs. This is a very pragmatic definition, clinically relevant for physicians caring for patients undergoing cardiac surgery. As the relevance of the primary endpoint depends on its definition, we insist on external validity and the objective way of diagnosing each PPC used in the composite endpoint of this trial. We have chosen to exclude pneumothorax and to evaluate it as an adverse event because high PEEP may increase the incidence of pneumothorax (barotrauma or surgical trauma). Cardiogenic pulmonary edema is considered to be an extrapulmonary complication because it may bias the primary outcome regarding the potential high incidence of this event in patients with chronic heart diseases. We insist on strict confirmation of cardiogenic edema with high left atrial pressure estimated with echocardiography or a pulmonary artery catheter. Nonetheless, pneumothorax and cardiogenic pulmonary edema might lead to the primary outcome discovering whether or not they lead to hypoxemia. The need for non-invasive ventilation or high-flow nasal oxygen therapy has not been included in the primary outcome because of the absence of defined indications in the standard procedures of the trial. Curative non-invasive ventilation or high-flow nasal oxygen therapy are used depending on local protocols or the physician’s discretion. Therefore, it will be recorded as a secondary outcome. By not allowing prophylactic use (in the absence of hypoxemia) of these techniques, we avoid a potential interaction with the primary outcome. Finally, we will evaluate postoperative extra-pulmonary complications because PPCs may be related to other organ failures, such as sepsis, postoperative atrial fibrillation or acute kidney injury. Evaluating different surgical complications (such as acute postoperative bleeding with a need for re-intervention, pericardial tamponade, wound infection, or the need for high doses of inotropes) will give a safety point of view on the surgical impact of the open-lung approach.

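### Two item definitions in the primary endpoint fail as written: the respiratory-failure grades omit hypoxemic patients moved straight to HFNO or NIV or never corrected, and pneumonia culture thresholds are per mm³, 1000 times the same numbers per mL

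*Protocol article*

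**What the plan says.** All references are to the protocol article.

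**Respiratory failure (Study endpoints).** The primary endpoint is met by any one of 13 items in the first 7 postoperative days. Three of the items are grades of respiratory failure, all excluding hypoventilation:

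- Mild: hypoxemia after 10 minutes on ambient air, corrected by 1–3 L/min through a nasal cannula.
- Moderate: hypoxemia despite 3 L/min, corrected by 4–10 L/min through a face mask.
- Severe: "Severe respiratory failure: SpO2 < 90% or PaO2 < 60 mmHg despite a 10 L/min oxygen supply with a face mask", corrected by more than 10 L/min, NIV, HFNO or invasive ventilation.

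**When the devices start (Follow up).** "The postoperative use of curative non-invasive ventilation or nasal high-flow oxygen therapy is implemented according to local protocols in each recruiting center". Only prophylactic use, before any respiratory failure, is barred.

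**Confirmed pneumonia (Study endpoints).** A new infiltrate plus a culture above "> 10^7^ CFU/mm^3^ on expectorated sputum, > 10^5^ CFU/mm^3^ on trans-tracheal aspiration", or above 10^4 CFU/mm³ on bronchoalveolar lavage.

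**Use of the items.** The secondary endpoints include each pulmonary complication analyzed individually by day 7.

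**The concern.** The three grades read as a ladder that covers every hypoxemic patient, but each rung carries two conditions joined by *and*. Only the top rung accepts NIV or HFNO as the means of correction, and it is reached only by failing 10 L/min. Nothing in the protocol requires a patient to pass through that step before a device is started. A compliant patient can therefore have respiratory failure in the protocol's own sense (otherwise the device would count as prophylactic and be barred) and yet score no grade of it. Whether a hypoxemic patient is graded then depends partly on local device policy.

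For pneumonia, the unit attached to the culture thresholds fixes which cultures count as confirmation. A unit wrong by three orders of magnitude would change what the item measures.

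At stake are the completeness of the composite and, more directly, the meaning of the separately reported respiratory-failure and confirmed-pneumonia endpoints.

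**Working it through.** **1. The ladder, tested path by path.** Inputs are the entry and correction conditions in Study endpoints and the device rule in Follow up.

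| Path | Mild | Moderate | Severe |
|---|---|---|---|
| Hypoxemic on room air, straight to HFNO or NIV | no: not corrected by 1–3 L/min | no: 3 L/min not failed, no 4–10 L/min mask | no: 10 L/min not failed |
| Hypoxemic on 3 L/min, straight to HFNO or NIV | no: not corrected by 1–3 L/min | no: not corrected by a 4–10 L/min mask | no: 10 L/min not failed |
| Hypoxemia never corrected by any means | no | no | no: correction is required here too |
| Fails 3 L/min, corrected at 5 L/min, later moved to HFNO | – | yes, already met | – |

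The first three paths meet no grade. The fourth shows that the gap does not reach everyone who ends on HFNO or NIV: a patient first corrected at a lower step has already been counted.

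**2. Routes back into the composite.** Postoperative variables specifies two visits a day to day 7, with SpO2 and/or PaO2 measured after 10 minutes on room air at every visit. A patient in the first two rows can score mild at an earlier visit, or later during weaning, if 1–3 L/min then corrects the hypoxemia. Items with no correction clause can also apply: fast-track extubation failure or new invasive ventilation with PaO2/FiO2 < 300, post-extubation respiratory acidosis, suspected pneumonia, atelectasis and ARDS. No such route exists for an individual grade. If severe failure is missed, nothing else in the list supplies it.

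**3. Units.** 1 mL = 1000 mm³, so CFU/mL = 1000 × CFU/mm³.

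| Specimen | As written, CFU/mm³ | Same threshold, CFU/mL |
|---|---|---|
| Sputum | > 10^7 | > 10^10 |
| Trans-tracheal aspirate | > 10^5 | > 10^8 |
| Lavage | > 10^4 | > 10^7 |

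For example, a lavage at 10^5 CFU/mL is 10^5 / 1000 = 10^2 CFU/mm³ and fails the written threshold of 10^4.

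**4. The plan's own figure, and what missed events would do to it.** Sample size and power gives 80% power for "25% in the control strategy group vs 15% in the experimental strategy group" with 247 per group; Statistical analysis makes the test two-sided at 5%.

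- Unpooled formula: n = (1.960 + 0.842)² × (0.25×0.75 + 0.15×0.85) / 0.10² = 7.849 × 0.315 / 0.01 = 247.2 per group. The 494 reproduces to within rounding; the pooled formula gives 250.
- Power at 247 per group, with pooled variance under the null: Φ[(0.10 − 1.960·√(2×0.20×0.80/247)) / √(0.315/247)] = Φ[(0.10 − 0.0705)/0.0357] = 79.5%.
- Illustration only: assume that the planning rates count every hypoxemic patient and that the same share of events is missed in both arms. The documents give no such share.

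| Share missed (assumed) | Rates | Power |
|---|---|---|
| 0% | 25.0% vs 15.0% | 79.5% |
| 2% | 24.5% vs 14.7% | 78.5% |
| 5% | 23.75% vs 14.25% | 76.9% |
| 10% | 22.5% vs 13.5% | 74.1% |
| 20% | 20.0% vs 12.0% | 68.0% |

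**The case against.** The best defense is that the composite is robust to gaps in single items. Any one of 13 items suffices, the room-air test is repeated twice a day, and very ill patients tend to have other routes in. For pneumonia, the suspected form needs the same infiltrate plus two signs, among them purulent secretions and antibiotic treatment, so many unconfirmed cases still count. Randomization is stratified by center, which balances local device policy across arms, and the outcome assessor is masked. The definitions also follow earlier trials and were kept for comparability. All of this stands as far as the composite is concerned. It does not rescue the individual endpoints, and it makes the gap in the grades smaller without closing it.

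Three stronger readings are tempting, and the documents support none of them.

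- *That the Discussion contradicts the endpoint definition.* It states: "The need for non-invasive ventilation or high-flow nasal oxygen therapy has not been included in the primary outcome because of the absence of defined indications". Within the severe grade, NIV and HFNO are two of four ways of correcting hypoxemia that has already persisted at 10 L/min. Their use alone never qualifies a patient, so the two passages agree.
- *That the loss can be stated in percentage points, or differs by arm.* This would need the share of patients escalated early and the share of those with no other item. The protocol gives neither, nor any figure on escalation by arm.
- *That confirmed pneumonia will be almost absent.* This would need culture densities that are not given. Nor does the protocol say that CFU/mL was intended; that inference rests on general laboratory convention and needs the sponsor's confirmation.

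**Conclusion.** Both faults hold at the level of the item definitions.

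The respiratory-failure grades are not exhaustive. Direct escalation to HFNO or NIV from room air or 3 L/min, and hypoxemia that is never corrected, fall outside all three. This follows from the text and needs no assumption beyond local protocols permitting such escalation, which the protocol allows. The individual respiratory-failure endpoints are affected directly. The composite is affected by an amount that cannot be quantified from the documents and is reduced by the other routes. The power figures only show sensitivity: with 79.5% at the planned size there is little reserve, but no particular loss is established.

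The culture thresholds are exactly 1000 times the same numbers per mL. If the laboratories report per mL and the thresholds are applied literally, confirmed pneumonia is set far too strictly as a secondary endpoint, with a smaller effect on the composite. The sample size calculation itself is not in question.

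**What to change.** **Respiratory failure.** For the composite, count any SpO2 < 90% or PaO2 < 60 mmHg, excluding hypoventilation, documented after 10 minutes on room air or on any oxygen support, whatever means corrected it and whether or not it was corrected. Grade mild, moderate or severe by the oxygen step at which hypoxemia was documented. Report direct escalation to NIV or HFNO as a category of its own. Do not grade by the highest support received, since that would let local device policy define the severe grade. Report the published definition as a sensitivity analysis.

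**Pneumonia.** Ask the participating laboratories which unit they report. If it is per mL, correct the three thresholds to CFU/mL in the protocol and wherever they are applied.

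**Cost.** One derivation rule, one added category, one sensitivity analysis and a unit check, with no change to patient care. SpO2 and/or PaO2 are already measured at every visit, and NIV and HFNO use is already recorded as a secondary endpoint; the oxygen step at each hypoxemic episode must be available in the case report form. The composite rate may rise slightly, and the definition moves a little away from the cited trials, which the sensitivity analysis covers. The article states that recruitment is under way, so the rule should be fixed and dated before any comparison by arm.
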